### Follow up schedule and data collection

A total of at most 14 visits will be scheduled. Data to be collected at each visit are summarized in Table 1.

**Table 1 Tab1:** Follow up schedule and data to be collected

Study period	Induction treatment stage		Randomized stage										Early exit
Visit	S1	S2-4	V0	V1	V2	V3	V4	V5	V6	V7	V8	V9	
	Wk0	Wk 4\8\12	Wk0	Wk4	Wk8	Wk12	Wk20	Wk28	Wk36	Wk44	Wk52	Wk60	
ICF	√												
Demographic data	√												
Past history and medication history collection	√												
Physical examination	√	√ √	√	√	√	√	√	√	√	√	√	√	√
Urine βHCG (if applicable)	√												
BCC, renal function, liver function, ESR,CRP,RF	√	√	√	√	√	√	√	√	√	√	√	√	√
Assessment committee examination	√	√ √	√	√	√	√	√	√	√	√	√	√	√
IC/EC judgement	√												
Randomization		√											
Hand X-ray-ran	√		√									√	√
Ultrasound of double hands	√		√									√	√
Anti-CCP antibody	√											√	√
Cost of exam and treatment	√		√	√	√	√	√	√	√	√	√	√	√
HAQ-DI/EQ-5D	√		√			√						√	√
Study Medication record	√	√	√	√	√	√	√	√	√	√	√	√	√
Concomitant medication record	√	√ √	√	√	√	√	√	√	√	√	√	√	√
AE record	√	√ √	√	√	√	√	√	√	√	√	√	√	√

*ICF* informed consent form, *BCC* blood cells count, *ESR* erythrocyte sedimentation rate, *CRP* c reactive protein, *RF* rheumatoid factor, *IC/EC* inclusion criteria/exclusion criteria, *Anti-CCP antibody* anti-cyclocitrulline polypeptide antibody, *HAQ-DI/EQ-5D* Health Assessment Questionnaire Disability Index/ Euro Qol five dimensions questionnaire, *AE* adverse event

Patients will be requested to return the residual drugs to obtain new drugs at each visit. Laboratory tests must be performed in the eligible study centers. These strategies were designed to improve adherence of subjects.

Subjects who relapse or cannot tolerant adverse effects before the end of the trial should exit the trial and receive empirical treatment, including but not limited to, other biological agents, or csDMARDs combination therapy. All patients who exit early will be kept in following up for the safety and cost-effectiveness analysis.

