### Eligibility criteria

Inclusion criteriaFulfill the 2010 EULAR/ACR diagnostic criteria of RA;Disease duration > 6 months;≥18 and≤70 years old;Use of single or combination of csDMARDs with standard dosage (must including MTX and/or leflunomide) for more than 3 months;DAS28-CRP> 3.2;Sign informed consent form (ICF).Exclusion criteriaReceive therapies of any of the below:Large surgical operations within 8 weeks (including articular operation) or in plan;Any former use of cell elimination therapy, including CAMPATH, anti-CD4, anti-CD5, anti-CD3, anti-CDl9, anti-CD20 and the research drug in the current study;γ-immunoglobulin, plasmapheresis, retuximab or IL-6 inhibitor within 6 months;Any form of glucocortocoid injection therapy within 4 weeks;Live vaccines or live attenuated vaccines within 4 weeks;Any alkylating agents including cyclophosphamide and nitrogen mustard, or total lymphoid irradiation therapy;Complicate with any other diseases or organ/tissue damages as follows:Autoimmune diseases other than RA. Patients combining with primary SjÖgren syndrome (pSS) are permitted;Severe or uncontrolled cardiac disease, nervous system disease, pulmonary disease (including chronic obstructive pulmonary disease and interstitial lung disease), renal disease, liver disease, endocrine disease (including diabetes mellitus) and gastrointestinal disease;Diseases that need oral or injection therapy of glucocorticoid, including but not limited to bronchial asthma, psoriasis and inflammatory bowel disease;Current or relapsing infections (include but not limited to tuberculosis or atypical mycobacterium disease, granuloma in chest X ray, type B or type C hepatitis, human immuno-deficiency virus (HIV), Zoster, but patients with nail fungal infection are permitted). Infection that needs hospitalization or intravenous antibiotics within 4 weeks, or oral antibiotics within 2 weeks;Malignant disease, including solid tumor and hematological malignancies (but patients with moved or cured skin basal cell carcinoma are permitted);Nerve damage or other painful disease that may affect pain evaluation;Laboratory abnormalities:Serum creatinine> 130umol/L;Alanine aminotransferase (ALT) or aspartate transaminase (AST) > 2 upper limit of normal, or total bilirubin> upper limit of normal;Platelet <100 × 109/L, or white blood cell count (WBC) <3 × 109/L;Interstitial lung disease: confirmed by chest X ray;Double hands X ray shows ACR imaging stage IV;Allergic to or have severe adverse reaction with any experimental drug in the induction or randomization stage;Pregnant or plan to be pregnant in 2 years, or nursing mothers.

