### Randomization

The blocked randomization, stratified by study center and gender of patients, will be performed centrally when CR or LDA is achieved (V0, week 0). The staffs responsible for randomization will obtain the group allocation code from the Peking University Clinical Research Institute (PUCRI) through an Interactive Web Response System (IWRS).

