### Interventions

Enrolled subjects will receive oral MTX 10–20 mg once a week and subcutaneous injection of TNFi 50 mg once a week in the induction stage.

Patients who did not receive MTX before recruitment, will initiate MTX 10 mg per week at enrollment. In the induction stage, MTX will be allowed to be titrated up to 20 mg per week if the patient do not achieve DAS28-CRP ≤ 3.2.

The three treatment strategies at the randomized stage will be:

Group A: add HCQ 200 mg twice per day and SSZ 1000 mg twice per day for the first 12 weeks and then remove TNFi but continue MTX + HCQ + SSZ for the next 48 weeks (intervention group, triple therapy group);

Group B: maintain TNFi + MTX for all the next 60 weeks (control group 1, TNFi maintenance group);

Group C: maintain TNFi + MTX for the first 12 weeks and then remove TNFi but continue MTX monotherapy for the next 48 weeks (control group 2, MTX monotherapy group).

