### Exit criteria

Patients or their authorized representative require withdrawal from the study;Do not achieve DAS28-CRP < 3.2 by the end of 12 weeks in the induction treatment;Relapse during the randomized phase;Because of AE or SAE, the responsible physician considers that the patient is not suitable to continue the trial;Because of protocol violation (PV), the responsible physician considers that the patient is not suitable to continue the trial;Become pregnant.

Participants will be advised verbally and in writing that they will be free to withdraw at any stage upon request.

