Once approved, the study protocol may not be changed at will. In case the protocol must be verified, the principle investigator, the responsible person of clinical research center and the principle investigators at all sites should discuss and agree on the updates. When an agreement is achieved, protocol revision note should be formulated and signed, and the revised protocol should be submitted to the IRB for approval before implementation.

To guarantee the quality of the study, all the staffs should receive a standard training before start of the trial, including good clinical practice (GCP), subject protection and ethical requirements, study protocol, standard operation procedures, CRF filling instructions, and standard assessment method of disease activity. The project training will run throughout the whole process of the study. The investigators and the study coordinators can add training contents according to actual need.

Treatment that changes during the whole study period will be recorded. To guarantee the correct injection method, each injection of TNFi will be performed in the study centers by medical staffs rather than at home by patients themselves.

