### Trial status

The current trial is ongoing and a total of 123 patients have been recruited into the second stage for randomized trial.

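### Table 1 schedules one pregnancy test, at S1, which is 4 to 12 weeks before randomisation; none follows while MTX continues in all arms

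*Protocol article*

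**What the plan says.** Pregnancy bars participation at two points. The exclusion criteria list "Pregnant or plan to be pregnant in 2 years, or nursing mothers" (Eligibility criteria), and the exit criteria list "Become pregnant" (Exit criteria).

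The schedule behind these rules is Table 1, which the article presents as the summary of what is collected at each visit. The row "Urine βHCG (if applicable" has a single tick, at S1. The columns S2-4, V0 to V9 and early exit are blank. The row "IC/EC judgement" is likewise ticked only at S1.

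Allocation comes later: it "will be performed centrally when CR or LDA is achieved (V0, week 0" (Randomization). All patients take MTX from induction onwards. Group A then adds HCQ and SSZ and stays on triple therapy, group B stays on TNFi plus MTX, and group C is to "maintain TNFi + MTX for the first 12 weeks and then remove TNFi but continue MTX monotherapy for the next 48 weeks" (Interventions). MTX is therefore scheduled to week 60 in every arm unless the patient relapses or exits.

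**The concern.** The protocol sets a rule for the whole course of treatment but schedules one check, before induction treatment. Nothing in the schedule re-checks the pregnancy exclusion at randomisation, and nothing later supports the exit rule except suspicion or the patient's own report. Suspicion is a weak substitute here, because nausea and vomiting are listed both as expected adverse events and as patient-reported outcomes (Study outcomes), so early signs of pregnancy can be put down to the drugs.

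Followed as written, a woman who conceives during induction can be allocated, possibly to a group that adds two further drugs, and continue on study medication. A test before allocation would prevent the randomisation. Found afterwards, the same pregnancy becomes a post-randomisation exit that stays in the intention-to-treat comparison. The main issue is participant safety; the analysis consequence is secondary.

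**Working it through.** The plan states no figure to reproduce. The check reads the tick positions in Table 1 and adds visit weeks.

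**Inputs**
- Only βHCG test: S1, induction week 0 (Table 1).
- Possible randomisation times: S2, S3 or S4, at induction weeks 4, 8 or 12 (Table 1). Patients move to the randomised stage as soon as they reach the target (Eligibility criteria, closing paragraph; Randomization).
- Length of the randomised stage: 60 weeks (Study design; Interventions).
- Visits after randomisation: weeks 4, 8 and 12, then every 8 weeks to week 60 (Table 1).
- Planned total: 240 (Sample size estimation). At the time of writing, "a total of 123 patients have been recruited into the second stage" (Trial status).

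**Age of the only test**

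Gap to randomisation = induction visit week. Gap to end of treatment = induction visit week + 60.

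| Target reached at | Weeks from test to V0 | Weeks from test to week 60 |
|---|---|---|
| S2 | 4 | 4 + 60 = 64 |
| S3 | 8 | 8 + 60 = 68 |
| S4 | 12 | 12 + 60 = 72 |

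The last column applies to patients who complete. It is shorter for those who relapse, whom the sample-size section expects to be 50% in group A and 74% in group C.

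**Visits with a test:** of the nine visits V0 to V8, after which study drug continues, 0 carry a tick in this row.

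**Is the tick position reliable?** The neighbouring rows keep their later ticks: routine bloods at every visit, and hand X-ray and ultrasound at S1, V0, V9 and early exit. A tick lost in extraction is therefore unlikely.

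**Contact between visits.** TNFi is given weekly (Interventions), and "each injection of TNFi will be performed in the study centers by medical staffs rather than at home by patients themselves" (Discussion). That adds weekly contact during induction, to week 12 in all arms, and to week 60 in group B. After week 12, groups A and C have only the 8-weekly visits.

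**Effect of the change.** With a test at V0 to V8, the age of the last test at allocation falls from 4, 8 or 12 weeks to 0. After randomisation the longest interval without a test is 8 weeks. The induction interval of 4 to 12 weeks stays untested unless S2-4 is ticked as well.

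**Number of tests**
- Still to be randomised: 240 − 123 = 117.
- V0 only: 117 × 1 = 117 strips at most.
- V0 to V8: 117 × 9 = 1,053 strips at most.

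These are ceilings: they treat every patient as applicable and assume that none leaves early. Tests at V1 to V8 for patients already randomised and still on treatment would be extra; their number is not given.

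**The case against.** The strongest reply is that nothing here is an error. The exclusion, the exit rule and the schedule do not contradict one another, and no section sets a testing frequency that Table 1 fails to meet. The article condenses a longer protocol, which may require repeat or for-cause tests and contraception. This stands in part: the point is a design improvement, and if the full protocol does test later, only Table 1 needs correcting. But the article does not leave the subject out. It prints a schedule that contains the row and ticks it once.

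Second, the exclusion also covers women planning pregnancy within 2 years, 2 × 52 = 104 weeks, which is longer than the 72-week maximum course. Every visit includes a physical examination and an adverse-event record, and the weekly injections add contact. These safeguards reduce the risk. They do not cover an unplanned pregnancy that has not been noticed, and none of them is a test.

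Third, a V0 test cannot prevent exposure during induction, because all patients take MTX from the start of that stage and only group A receives new drugs at V0. A pregnancy recognised during induction would already lead to exit. Both statements are correct. The benefit at V0 is to find the unrecognised case, stop further exposure and avoid the randomisation.

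Fourth, no harm is quantified, and pregnancies that begin before allocation would be balanced between arms on average. That is also correct, so no bias in the primary comparison is claimed. Finally, recruitment was to close by 30 September 2021, so 117 is an upper limit on the patients whom a V0 test could still reach.

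**Conclusion.** The concern holds. As scheduled, the only pregnancy test is 4, 8 or 12 weeks old at randomisation and up to 72 weeks old at the end of treatment, with no test at any of the nine visits V0 to V8. This is a cheap safety improvement that should be made, not a contradiction, and it leaves sample size, power and alpha unchanged.

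The conclusion assumes that Table 1 is the operative schedule and that patients reach the target at a scheduled induction visit. Entry is open from age 18 to 70 without restriction by sex, so some women who could become pregnant are eligible; how many is not stated. The case rests on the protocol's own rule that pregnancy is incompatible with participation and needs no outside figure on drug toxicity. Confidence is medium, because the full protocol is not shown.

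**What to change.** Tick the existing βHCG row at V0 and require the result before the allocation code is obtained from the web response system. Tick it also at the later visits where study drug is dispensed for continued treatment (V1 to V8), identically in all arms; the sponsor can set the exact later frequency. A positive result before allocation means no randomisation. A later positive result is handled under the existing exit criterion, with the follow-up already planned for patients who exit early.

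The cost is a few ticks in one row and a urine strip at existing visits for applicable patients, with no new visit or staff. The downsides are a small consumable cost, a minor burden for these patients, and a protocol revision note agreed by the site investigators and approved by the IRB, which can go with the next amendment. The V0 test helps only patients not yet randomised; the later tests also help those still on treatment.

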### Study outcomes

The primary outcome will be disease relapse, which is defined as DAS28-CRP increases by at least 0.6 compared with that at randomization and is greater than 3.2 simultaneously.

The secondary outcomes will include the following: the incremental cost per reducing 1 case of relapse; change of disease activity score from baseline, assessed by DAS28-CRP, DAS28-ESR, CDAI and SDAI, at 60 weeks after randomization; duration of maintaining CR or LDA after randomization; change of hands X ray modified Sharp score at 60 weeks after randomization; ultrasound remission of hands at 60 weeks after randomization; Health Assessment Questionnaire Disability Index (HAQ-DI) and health related quality of life [the five-levele EuroQol-5D-5L (EQ-5D-5L) and short form-6D (SF-6D)] at 60 weeks after randomization; adverse events and complications; and patient reported outcomes (PRO) including rash, nausea, vomiting, diarrhea, abdominal pain and fever.

All outcomes will be measured after 60 weeks.

Responsible physicians will monitor and record any adverse events (AEs) during the whole trial. Expected AEs will include: allergy; ALT and AST elevation; hemocytopenia; infection; digestive tract symptom including nausea and vomiting; and hemorrhage of digestive tract defined by fecal occult blood positive, etc. In case of AEs, symptomatic treatment or reduction of drug dosage or even discontinuation of drugs will be carried out when necessary. If the drugs is tapered or discontinued, a serious AE will be considered and the patient should exit the study. Physicians will assess the association between intervention and AEs on a 6-point scale (1 = definitely related; 2 = probably related; 3 = possibly related; 4 = probably not related; 5 = definitely not related; 6 = unknown). All AEs will be categorized into three levels using the Spilker classification [(1) mild = not need additional intervention, nor significantly inhibit normal life function of the participant; (2) moderate = significantly inhibit the normal life function of the participant, and may need additional intervention, recovering afterwards; and (3) severe = require intensive intervention, and leave sequelae).

Serious adverse event (SAE) is defined as any of the following conditions: (1) threat to life; (2) lead to hospitalization or extend hospital stay; (3) lead to permanent or notable disability or functional disorder; and (4) lead to taper or discontinue the study drugs. In case of SAE or scheme violation during study duration, the relevant Institutional Review Board (IRB) and the leading study site (Peking University First Hospital) will be informed and will decide whether the trial will continue or not. Patients will be followed even if protocol has been breached for any reason. The SAE will be recorded as safety outcome.

An independent assessment committee will be set up for outcomes evaluation. The assessment committee will be blinded to the treatments. However, in case of “SAE”, unblinding will be permitted.

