#### Concomitant medication permitted

NSAIDs will be permitted, but the drug name, dosage and time of treatment should be recorded.

Anti-hypertension medications, anti-diabetic agents, aspirin and β-blocker will be permitted.

All the concomitant medications used during the study should be recorded in the case report form (CRF).

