**Fig. 2 Fig2:**
[figure not shown]
The decision tree model of the study. RA: Rheumatoid Arthritis; MTX: methotrexate; HCQ: hydroxychloroquine; SSZ: sulfasalazine

Non-parametric bootstrap will be used to calculate the 95% confidence interval of incremental cost effectiveness ratio and draw the cost-effectiveness acceptability curve. The factors which may affect the analysis results will be evaluated by one-way and probability sensitivity analysis. All the analysis will be performed by TreeAgePro11.0 software.

Safety analysis will be performed based on the safety set (SS). The incidence of AEs and SAEs related to the study will be described. Crosstabs will be constructed to map the changes of laboratory index.

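### Digestive-tract hemorrhage is defined by a positive occult blood test that the published visit schedule does not include, so its incidence mixes laboratory positives with bleeding and depends on how often patients are tested

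*Protocol article*

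**What the plan says.** In the protocol article, Study outcomes gives an open-ended list that begins "Expected AEs will include: allergy; ALT and AST elevation; hemocytopenia; infection" and goes on to digestive symptoms and "hemorrhage of digestive tract defined by fecal occult blood positive". The list ends with an etcetera. Adverse events and complications are a secondary outcome; hemorrhage is not named as an outcome of its own.

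On collection, Follow up schedule and data collection states: "Data to be collected at each visit are summarized in Table 1". The main laboratory row of that table reads "BCC, renal function, liver function, ESR,CRP,RF" and is ticked throughout the randomized stage and at early exit. Urine HCG and anti-CCP antibody have rows of their own. No row mentions stool or occult blood.

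On who detects events: "Responsible physicians will monitor and record any adverse events (AEs) during the whole trial". On blinding: "The assessment committee will be blinded to the treatments". Nothing is said about blinding the treating physicians.

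On analysis, the safety paragraph that closes Statistical analysis says: "The incidence of AEs and SAEs related to the study will be described". It uses the safety set and plans no test or decision rule for hemorrhage.

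**The concern.** The definition equates a screening test with a clinical event. Taken literally, it errs in both directions: a well patient with a trace of blood in one stool sample counts as having had a hemorrhage, and a patient with a visible bleed and no stool test does not.

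The other laboratory-based events in the same list, raised transaminases and low blood counts, rest on tests done at every randomized-stage visit in every arm. Hemorrhage rests on a test that the published schedule does not contain. Its frequency is then partly a record of testing habits. A physician who knows the treatment might test more readily in one arm, for example where digestive complaints are more common, and Group A adds two oral drugs to methotrexate. The table of adverse events by arm could then show a difference in hemorrhage that reflects testing alone. Safety is part of the trial's stated aim, so a reader will look at that row.

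**Working it through.** The article gives no bleeding rate, no occult-blood positivity and no testing frequency, so there is no figure of the plan to reproduce. The check has two parts.

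**1. The definition against the schedule and the recording rules**

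| Case | Does it meet the hemorrhage definition? | Is it recorded as an adverse event? |
|---|---|---|
| Trace-positive stool, no clinical bleeding | Yes | Yes, as hemorrhage |
| Overt bleed, stool test positive | Yes | Yes, as hemorrhage |
| Overt bleed, no stool test | No | Yes, but under some other term |
| Trace blood, no stool test | No | No |

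The first row is a mislabelled event. The third is a bleed that is kept but filed elsewhere. Whether a patient with trace blood falls in the first row or the last is decided by testing alone, and Table 1 does not fix testing.

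**2. What unscheduled testing does to the described incidence**

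Inputs: 80 patients per arm (Sample size estimation). *Assumptions, not in the article:* positivity q = 5% to 10%, the same in both arms; share of patients tested t = 10% to 50%; within an arm, being tested is unrelated to being positive.

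Observed incidence = q × t. Expected count = 80 × q × t. The ratio between two arms with equal q is t₁ / t₂.

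| Tested, arm 1 / arm 2 | Observed at q = 5% (patients of 80) | Observed at q = 10% (patients of 80) | Ratio |
|---|---|---|---|
| 100% / 100% | 5% / 5% (4.0 / 4.0) | 10% / 10% (8.0 / 8.0) | 1.0 |
| 30% / 30% | 1.5% / 1.5% (1.2 / 1.2) | 3% / 3% (2.4 / 2.4) | 1.0 |
| 50% / 20% | 2.5% / 1.0% (2.0 / 0.8) | 5% / 2% (4.0 / 1.6) | 2.5 |
| 40% / 10% | 2.0% / 0.5% (1.6 / 0.4) | 4% / 1% (3.2 / 0.8) | 4.0 |

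Under these assumptions, incomplete testing always lowers the observed positivity over all patients. It distorts the comparison between arms only when the shares tested differ.

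Using the number tested as denominator removes the distortion in this illustration. At q = 5% with 50% and 20% tested, 80 × 0.50 = 40 and 80 × 0.20 = 16 patients are tested, and the rates are 2.0/40 = 5% and 0.8/16 = 5%, a ratio of 1.0. If physicians test mainly patients whom they suspect of bleeding, this denominator does not fully restore comparability, but it shows the reader how much testing lies behind each count.

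**The case against.** The case against giving this weight is substantial, and most of it stands.

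- **Overt bleeds are not lost.** A reader might infer that the definition lets real bleeds go unrecorded. It does not: physicians record any adverse event throughout the trial and the expected list is open. A bleed that threatens life, leads to hospitalization, or leads to study drugs being reduced or stopped also meets the article's definition of a serious adverse event. Only the category label is wrong.
- **The rate by arm is not shown to be uninterpretable.** A reader might infer this from the missing stool test. The comparison is biased only if testing differs by arm, and nothing in the article says that it does. The permission for NSAIDs ("NSAIDs will be permitted, but the drug name, dosage and time of treatment should be recorded") applies to all arms and gives no reason for a difference between them.
- **Large counts of false hemorrhages can be produced, but only from an extreme contrast.** Suppose 1% to 5% of tests are positive without bleeding, independently across tests. Three tests per patient then give 1 − 0.99³ = 3.0% to 1 − 0.95³ = 14.3%, or 80 × 0.030 = 2.4 to 80 × 0.143 = 11.4 patients per arm. Setting that against an arm in which nobody is tested has no basis in the article.
- **The event carries little formal weight.** It is one example in a list, reported descriptively.
- **The article is condensed.** Tests prompted by an event often do not appear in a visit schedule, and the full protocol may say when stool is tested. The absence of the test is established only for the published Table 1.

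What the objection does not remove is the stated definition. It equates a positive test with a hemorrhage whatever the full protocol says about timing. Scheduled testing in all arms would even out detection but would not turn a trace positive into a clinical bleed.

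**Conclusion.** The point holds as a minor defect in safety reporting. The article fixes the event badly: it labels a laboratory result as hemorrhage, leaves an overt bleed without a stool test outside the category, and ties the count to a test that its own schedule does not contain and that physicians not stated to be blinded would decide to order.

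The size for this trial cannot be stated, because neither positivity nor testing frequency is given. The spurious ratios of 2.5 and 4.0 show what unequal testing could do under assumed inputs; they do not estimate what will happen. With equal testing the ratio stays at 1.0. At the assumed rates the expected counts in the unequal-testing scenarios are at most four patients per arm, so even a large ratio would rest on few events.

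The primary outcome, relapse by DAS28-CRP, and the sample size are not affected.

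**What to change.** In Study outcomes, count digestive-tract hemorrhage as overt or diagnosed bleeding, whether or not a stool test was done. Report a positive occult blood test separately as a laboratory finding, with the number of patients tested in each arm as its denominator. No new stool testing is needed.

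The cost is modest but goes beyond a change of wording. Under the rules for protocol changes in the Discussion, the site investigators must agree, a revision note must be signed, and the IRB must approve before implementation. Events already recorded among the 123 patients randomized at the time of the article (Trial status) would need recoding. Some of those records may lack the detail needed to separate a positive test from a clinical bleed; these should be reported as unclassifiable, by arm.

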**Methods:**

It will be a two-stage trial. In the first stage, all RA patients who failed to csDMARDs treatment [disease activity score 28 (DAS28)-CRP > 3.2] will receive MTX plus TNFi for no more than 12 weeks. Patients achieving DAS28-CRP < 3.2 during the first stage will be randomized into three groups at 1:1:1 ratio: (A) add hydroxychloroquine (HCQ) and sulfasalazine (SSZ) for the first 12 weeks and then remove TNFi but continue other treatments for the next 48 weeks; (B) maintain TNFi + MTX for 60 weeks; and (C) maintain TNFi + MTX for the first 12 weeks and then remove TNFi but continue MTX monotherapy for the next 48 weeks. The primary outcome will be disease relapse (DAS28-CRP increases by at least 0.6 and > 3.2). Secondary outcomes will include the incremental cost per reducing 1 case of relapse; patient reported intolerance to the treatment; adverse events; change of mean disease activity measured by DAS28, clinical disease activity index (CDAI) and simplified disease activity index (SDAI); the proportion of modified Sharp score increase < 0.3; ultrasound-detected remission in hands; Health Assessment Questionnaire Disability Index (HAQ-DI) and health related quality of life [the five-level EuroQol-5D (EQ-5D-5L) and short form-6D (SF-6D)].

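### Every adverse event that leads to a dose taper or stop counts as an SAE, so the reported SAE incidence will mix tolerability and laboratory-led dose changes with serious harm

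*Protocol article*

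**What the plan says.** All of this is in the protocol article.

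- **Study outcomes, SAE definition.** An event is serious if it meets any of four conditions: threat to life; hospitalisation or a longer stay; permanent or notable disability or functional disorder; and "4) lead to taper or discontinue the study drugs".
- **Study outcomes, handling of adverse events.** The same rule appears as an instruction: "If the drugs is tapered or discontinued, a serious AE will be considered and the patient should exit the study". The sentence before it names dose changes among the ways of managing an adverse event: "reduction of drug dosage or even discontinuation of drugs will be carried out when necessary". The expected events include nausea, vomiting, ALT and AST elevation and low blood counts.
- **Statistical analysis, safety paragraph.** "The incidence of AEs and SAEs related to the study will be described".
- **Study outcomes, reporting.** After an SAE the IRB and the leading site "will be informed and will decide whether the trial will continue or not".
- **Study outcomes, masking.** The assessment committee is blinded, but in case of an SAE "unblinding will be permitted".
- **Abstract and Study outcomes, tolerability.** The abstract lists "patient reported intolerance to the treatment" as a secondary outcome. Study outcomes lists patient-reported rash, nausea, vomiting, diarrhoea, abdominal pain and fever.
- **Interventions.** Group A is to "add HCQ 200 mg twice per day and SSZ 1000 mg twice per day for the first 12 weeks" on top of TNFi and MTX, and then continues on three drugs without TNFi.

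**The concern.** Three of the four conditions describe what happened to the patient. The fourth describes what the physician did with the drug. Once they are pooled, a reader who sees an SAE incidence cannot tell how much of it is serious harm. A high figure may be mostly dose changes. Two equal figures may hide unequal serious harm.

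Safety is one of the trial's stated aims, and the SAE line is the one most readers look at first. The mix could also differ by arm, since group A takes more drugs than the others.

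The label has a second use. It is the stated ground for an exception to the masking of the assessment committee, the only party the article describes as blinded. A broad label makes that exception broad.

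**Working it through.** **No figure to reproduce.** The article gives no rate for AE-led tapers or stops, for SAEs or for unblinding. The sample size rests on relapse alone and is not touched.

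**Step 1: is the rule really this wide?** The definition and the instruction in Study outcomes agree with each other, so a slip of wording is unlikely. Neither sets a threshold. The planned removal of TNFi at week 12 in groups A and C is not caused by an adverse event, so it is not caught.

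**Step 2: what could the dilution be?** Let *s* be the share of patients meeting any of conditions (1) to (3), and *t* the further share meeting only condition (4). The share of SAE patients with a dose change alone is *t* / (*s* + *t*). Both inputs are assumed; neither is in the document.

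| *s* (assumed) | *t* = 5% | *t* = 10% | *t* = 20% |
|---|---|---|---|
| 2% | 5/7 = 71% | 10/12 = 83% | 20/22 = 91% |
| 5% | 5/10 = 50% | 10/15 = 67% | 20/25 = 80% |

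In an arm of 80, *s* is 1.6 to 4 patients and *t* is 4 to 16. The dilution needs no difference between arms. The percentages only restate the assumed rates; they show how the label works and do not forecast anything.

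**Step 3: what could it do to a comparison of arms?** From Interventions, group A takes four drugs to week 12 and three afterwards, group B two throughout, and group C two and then one. Assume *s* = 3% in both A and C.

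| *t* in A v C (assumed) | Labelled SAEs, A v C | Gap |
|---|---|---|
| 10% v 10% | 13% v 13% | 0 points |
| 10% v 5% | 13% v 8% | 5 points |
| 15% v 5% | 18% v 8% | 10 points |

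Serious harm is equal in every row. Drug counts make a difference in *t* plausible but do not measure it: relapse stops study treatment, and relapse is expected in 50% of group A and 74% of group C (Sample size estimation), so actual exposure will fall short of plan by different amounts.

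**Step 4: the masking exception.** Table 1 schedules the committee's examination at early exit. If a dose change is an SAE and the patient then exits, unblinding is permitted at about the time that examination is due. The article does not say who may be unblinded, by whom, or whether before the examination. How many such exits there would be is also open: Study outcomes says tapered patients should leave, while Exit criteria leaves an AE-led exit to the physician's judgement.

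**The case against.** **The rule is open and consistent.** It is stated twice, and anyone who reads the definition knows what SAE means in this trial. That stands, and there is no contradiction. But a safety table is usually read without the definition beside it, and the pooled figure still cannot be taken apart by its reader.

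**Condition (4) does some work.** Stops for raised transaminases or low blood counts are expected events, and they are not among the patient-reported symptoms. Condition (4) brings them to notice. This stands, so the events should be kept and reported under their own name.

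**The events can be separated later.** Severity grades, causality ratings and medication records exist, and the safety analysis is descriptive. This also stands, and it is why the fix is cheap. It does not settle the matter, because the outcome the article defines and describes is the pooled one.

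**Notifying too much is cautious.** Review by the IRB and leading site is not an automatic stopping rule, and no harm from extra notices is shown. Prompt notification can continue.

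Some stronger readings are tempting, and the document does not support them:

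- *That the rule biases safety against triple therapy.* More dose changes on more drugs would be a real effect of the regimen. The fault is the name given to them.
- *That an event graded moderate yet counted as serious proves an error.* Severity and seriousness are different scales; a moderate event that led to hospitalisation would also be an SAE.
- *That unblinding distorts the relapse result.* It is permitted, not required. CRP is a laboratory value, and the article does not say how the exit DAS28-CRP enters the primary analysis.

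**Conclusion.** The concern holds for the meaning of the SAE incidence. As defined, that incidence combines tolerability and laboratory-led dose changes with serious harm and cannot be read as serious harm in any arm. This follows from stated text and rests on no assumed rate.

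The size is unknown. The 50-91% range and the gaps of 0 to 10 points hold only under the assumed rates above.

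The masking point is secondary and conditional: the wording allows the committee to be unblinded after a mere dose change, but no effect on relapse is shown. The sample size and primary comparison are unaffected. Severity is minor to moderate.

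**What to change.** 1. Define and report SAEs by outcome: death, threat to life, hospitalisation or its prolongation, lasting disability.
2. Report adverse events leading to dose reduction or discontinuation as a separate category by arm, including laboratory-led ones. Recode existing condition (4) records from the adverse event and study medication records that Table 1 collects at each visit. No new data are needed.
3. Keep prompt notification of these events to the IRB and leading site if the investigators value it.
4. State that a dose change alone does not permit unblinding of the assessment committee, and that the early-exit DAS28-CRP is recorded before any code is revealed to an assessor.

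The cost is a wording amendment through the process in the Discussion (agreement of the principal investigator, the research centre lead and the site investigators, a signed revision note and IRB approval), plus a small recode for patients already randomised, 123 of the planned 240 at the time of writing. Committee unblindings that have already occurred can only be listed. If an amendment is not wanted, tabulating SAEs by qualifying condition would cure the reading of the incidence but would leave the unblinding wording as it is.
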